### Eligibility

We will include adults (> 18 years old), males and females, with a medical diagnosis of T2DM and increased waist circumference (≥ 80 cm for women and ≥ 94 cm for men), with or without medication (including insulin treatment), with stable weight for three months prior to the start of study, who have received no change in dose of beta blocker or thyroxine for three months prior to the start of study, and no anticoagulant or oral steroid treatment. Inclusion criteria are present glycated hemoglobin (A1c) ≥ 6.0% (≥ 42.1 mmol/mol), with no upper boundary, creatinine < 130 μmol/L and liver enzymes less than four times above the upper reference value.

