## Methods/Design

### Participants

We aim to enroll 15 participants with T2DM, males and females, > 18 years old based, on the power calculations (see below) estimation of a required minimum of 13 patients, allowing for one or two drop-outs. Patients live in the island of Lanzarote, in the archipelago of Canary Islands (Spain), located off the western coast of Africa.

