**Figure 1 F1:**
[figure not shown]
Four-day weighed food record and satiety score sheet.

Regarding insulin titration, the participant’s physician will handle insulin titration as needed.

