## Consent

Once 15 interested persons contact the researchers, an initial meeting with the study investigators will be arranged to give additional information about the study. Additional eligible subjects will be placed in queue for possible participation in case of drop-out(s). People who are willing to participate in the study and who meet inclusion criteria (medical diagnosis of T2DM, increased waist circumference, stable body weight for three months prior to the start of study, stable dosing of beta blockers or thyroxine for three months prior to the start of study, and absence of chronic oral steroid treatment, and anticoagulant treatment) will receive written information about the study and informed consent as approved by the ethics committee. After returning the informed consent, laboratory tests for plasma A1c, creatinine and liver enzymes will be analyzed. For each person who is excluded or declines participation, one person from the queue will be contacted and informed individually.

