### Power calculations

The predefined primary outcomes are changes in fasting fructosamine and glucagon. In order to detect, with 80% power and at a significance level of 5%, a 26 μmol/L larger reduction in fructosamine after diet B than after diet A, 12 subjects are estimated to be required. For a 37 ng/L difference in change in fasting glucagon between the diets, 13 subjects are estimated to be required.

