### Intervention

The intervention is based on two diets: a) healthy diet A (healthy diet with cereal grains and dairy products), and b) healthy diet B (healthy diet without cereal grains and dairy products). After randomization, there will be no blinding to dietary assignment for study participants, nor for those administering the interventions or assessing the outcomes. Following randomization, all subjects will receive oral and written information about their respective initial dietary intervention. Owing to the fact that all participants in both groups will start the intervention at the same time, information about the specific intervention will be provided in group sessions, one for each group before the study starts. Prior to the beginning of the second dietary period, participants will be instructed about the new dietary intervention, in group sessions. Each session will last one hour and will be performed in the meeting room at the Hospital Insular de Lanzarote after the laboratory tests. The degree of behavioral support will be the same in both interventions in order to minimize differences in motivation. Written information with dietary advice, a seven-day menu plan and food recipes are similarly formulated for both diets. The rationale behind the higher intake of whole grains, dairy and legumes in healthy diet A is based on the possible beneficial effect of those foods in the treatment of T2DM in some studies [29], and their prominent position in Spanish dietary guidelines for patients with T2DM [30]. The rationale behind the exclusion of grains, dairy and legumes in healthy diet B is based on the observed positive effects in some previous studies [21,22].

Written information consists of a detailed seven-day meal plan with five meals per day and corresponding recipes (Additional file 3). Participants will be requested to follow the menu plan as much as possible when eating away from home. They will be requested to report (in as much detail as possible, the ingredients) any meal taken which differs from what is stipulated in the menu plan. In that case, they will be encouraged to photograph the meal, and send it to one of the investigators, whenever possible.

Advice about regular physical activity will be given equally to all subjects. Specifically, they will be recommended not to change their current physical activity during the whole trial.

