### Outcome assessment

#### Primary outcomes

The primary outcomes of this study are fasting fructosamine and glucagon. These outcomes will be determined after obtaining venous blood in the fasting state at start and end of each intervention period.

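### The three-month dose-stability rule names beta blockers and thyroxine but not glucose-lowering drugs, so a recent change in diabetes treatment can add avoidable noise to fructosamine

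*Protocol article*

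**What the plan says.** Under Eligibility, patients may enter "with or without medication (including insulin treatment"), and A1c must be at least 6.0% with no ceiling. The same section asks for stable weight over three months and limits the dose-stability requirement to patients "who have received no change in dose of beta blocker or thyroxine for three months prior to the start of study". The Consent section lists the entry criteria again and keeps the same scope: "stable dosing of beta blockers or thyroxine for three months prior to the start of study". Neither list mentions a stable glucose-lowering regimen.

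Under Primary outcomes, "The primary outcomes of this study are fasting fructosamine and glucagon", both measured at the start and end of each four-week period. The Power calculations section gives, for a 26 µmol/L "larger reduction in fructosamine after diet B than after diet A, 12 subjects are estimated to be required". The Participants section plans 15 patients from an "estimation of a required minimum of 13 patients, allowing for one or two drop-outs". During the trial, the participant's "physician will handle insulin titration as needed" (Procedure), and change in medication is recorded as a secondary outcome.

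**The concern.** The protocol accepts that a recent dose change can disturb the measurements, since it guards against this for two drug classes. Those two act less directly on glucose than the diabetes drugs that the rule leaves out.

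A patient who started, stopped or changed a diabetes drug shortly before entry may not have reached a new steady level of fructosamine when period 1 begins. The period 1 baseline removes whatever has already happened. What remains is the drift between that baseline and the week 4 measurement. By period 2, which starts at week 10, the drift will probably have lessened, so it need not cancel within the patient and becomes part of that patient's diet difference. Whether it favours diet A or diet B depends on the randomised order.

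Precision is at stake, in a trial whose planned minimum of 13 completers leaves little to spare.

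**Working it through.** **Inputs from the protocol article.** Target difference 26 µmol/L, 80% power, 5% level, 12 subjects (Power calculations); minimum 13, enrolment 15 (Participants); two-tailed tests (Data analysis).

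**Assumptions.** The test is a one-sample t-test on within-patient diet differences. A number k of completers drift by d µmol/L in period 1 and not in period 2. The documents give neither k nor d; the ranges used are k = 1 to 3 and d = 10 to 26.

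**Step 1: the plan's own figure.** No SD is stated, so 12 subjects cannot be reproduced independently. Solving the noncentral-t power equation for 80% at n = 12 gives an SD of the within-patient difference of 29.26. This is the largest SD for which 12 suffice; below 27.73, 11 would do. With 29.26, the standard error at n = 13 is 29.26/√13 = 8.11 and power is 83.6%. At n = 15, power is 89.2%.

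**Step 2: add the drift.** Because order is random, a drift d enters a patient's diet difference as +d or −d. Averaged over n completers, the widened SD is √(29.26² + (k/n)·d²). For k = 3, d = 26, n = 13: √(856.0 + 0.2308 × 676) = √1012.0 = 31.81.

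| k of 13 | d | SD | Increase | Power at n = 13 |
|---|---|---|---|---|
| 0 | – | 29.26 | – | 83.6% |
| 1 | 10 | 29.39 | 0.4% | 83.3% |
| 1 | 26 | 30.13 | 3.0% | 81.5% |
| 2 | 10 | 29.52 | 0.9% | 83.0% |
| 2 | 26 | 30.98 | 5.9% | 79.3% |
| 3 | 10 | 29.65 | 1.3% | 82.7% |
| 3 | 26 | 31.81 | 8.7% | 77.2% |

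**Step 3: check by simulation.** The formula treats the drift as extra normal variance, which is slightly pessimistic. Simulating trials with a 7:6 split of orders and a fixed drift in one direction gives about 83.5% for k = 1, d = 10; 80.3% for k = 2, d = 26; and about 78.7% for k = 3, d = 26. Type I error stays between 4.6% and 5.0%.

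**Step 4: full enrolment.** With three of 15 completers drifting by 26, the SD is √(856.0 + 0.2 × 676) = 31.48, and power by the formula is 84.4%.

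**Step 5: beyond the range.** Nothing in the documents caps the drift at 26. A drift of 40 in two of 13 gives an SD of √(856.0 + 0.1538 × 1600) = 33.20 and power of 73.7%. The result follows the assumption, so no single figure can be taken as the loss.

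**The case against.** The strongest case against is that the effect is small and hypothetical. At n = 13, power falls below 80% only if two or three patients each drift, after their baseline, by as much as the whole target effect; in simulation only three such patients do it. That stands. So does the point that the unstated planning SD may come from patients with similarly mixed treatment, in which case adding drift counts the same noise twice. In a 15-patient pilot, broad entry of medicated patients is also a defensible choice.

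A second objection is that exclusion can cost more power than it saves. Without replacement and without drift, power is 80.0% at n = 12, 75.7% at n = 11 and 70.6% at n = 10. Keeping one, two or three patients who drift by 26 gives 81.5%, 79.3% and 77.2% at n = 13. The arithmetic is right, but the Consent section says that each excluded person is followed up by contacting one from the queue. Replacement therefore answers the objection as long as the queue, whose size is not stated, is long enough. It matters because "all participants in both groups will start the intervention at the same time", which makes it hard to defer a candidate.

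Other provisions limit the problem without closing it. Stable weight does not exclude a recent drug change. Recording medication change as an outcome restricts nothing before entry. The period baselines remove only drift that is already complete.

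A reader might infer that the gap biases the comparison towards one diet. The documents do not support that: order is randomised, so drift has no systematic direction, and the simulated type I error is not inflated. A reader might also infer that the trial is underpowered because of it. That rests on assumed drift at the extreme of the range and on only 13 completers.

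**Conclusion.** The gap is certain from the text: both statements of the rule leave out the drug class most closely tied to fructosamine, and nothing else in the article keeps out a recently changed regimen. The consequence is avoidable noise in period 1, not bias, and its size cannot be derived from the documents.

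Under the assumed 10 to 26 µmol/L in 1 to 3 of 13 completers, the loss runs from under half a percentage point to about 5 (simulation) or 6 (formula). These figures rest on the back-solved SD, a paired analysis, and drift confined to period 1. With all 15 completing, even the worst case in that range keeps power above 84%.

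The point is worth considering because the remedy is cheap and extends a safeguard that the protocol already uses. It does not call the design into question.

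**What to change.** In both Eligibility and Consent, keep the existing rule and add: no start, stop or dose change of non-insulin glucose-lowering drugs, and no start, stop or change of insulin type or regimen, in the three months before study start. State a limit for permitted insulin dose adjustment, for example a prespecified percentage of total daily dose, so that eligibility does not turn on case-by-case judgement. The documents give no basis for the percentage, so the sponsor would have to choose it.

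Replace each excluded candidate from the queue so that enrolment stays at 15. The Consent section checks these criteria before the screening laboratory tests and randomisation follows later, so no randomised patient is lost.

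The cost is one clause in two places and a slightly smaller recruitment pool on one island. Insulin titration during the trial is a separate matter that an entry criterion does not address.

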### Procedure

The first 15 enrolled participants will undergo baseline tests, including A1c, creatinine and liver enzymes. At this time they will be instructed, in a group session, how to perform the four-day weighed food record and fill the satiety score sheets (Figure 1). Later, participants who meet the inclusion criteria will be notified about their final inclusion in the trial and reminded how to perform the four-day weighed food record and satiety score. Participants will borrow an electronic weighing scale with tare function and will be provided with enough sheets for the four-day weighed food record and satiety score. Five to seven days later, they will return the food records. The baseline four-day food record will yield information about the pre-study food choices and nutritional composition. The four-day food record and satiety score will be carried out at the start and end of each intervention period. After receiving the first food records, participants will be appointed for the first laboratory tests and intervention allocation. Based on total energy expenditure, as estimated by a bio-electrical impedance analyzer model BC-545 (Tanita Corporation, Tokyo, Japan), we will provide each participant with a menu plan with the approximate energy intake to avoid changes in body weight.

**Figure 1 F1:**
[figure not shown]
Four-day weighed food record and satiety score sheet.

Regarding insulin titration, the participant’s physician will handle insulin titration as needed.

### Randomization

The study participants will be randomly allocated to start with either diet A or diet B. The process will be performed after the first laboratory testing. Randomization will be performed by use of an Internet-based random sequence generator from the School of Computer Science and Statistics, Trinity College, Dublin [http://www.random.org/sequences/]. Due to the small sample size, and to avoid unbalanced allocation of the participants to one of the starting diets, stratified sampling by use of minimization technique will be used. Weighting variables are starting diet and duration of T2DM [28].

## Consent

Once 15 interested persons contact the researchers, an initial meeting with the study investigators will be arranged to give additional information about the study. Additional eligible subjects will be placed in queue for possible participation in case of drop-out(s). People who are willing to participate in the study and who meet inclusion criteria (medical diagnosis of T2DM, increased waist circumference, stable body weight for three months prior to the start of study, stable dosing of beta blockers or thyroxine for three months prior to the start of study, and absence of chronic oral steroid treatment, and anticoagulant treatment) will receive written information about the study and informed consent as approved by the ethics committee. After returning the informed consent, laboratory tests for plasma A1c, creatinine and liver enzymes will be analyzed. For each person who is excluded or declines participation, one person from the queue will be contacted and informed individually.

### Ethics committee and participants insurance

The ADILAN study was approved by the Ethics Committee of Clinical Investigation (CEIC) of the Hospital Universitario de Gran Canaria, Doctor Negrín (Code CEIC Negrín: 130030). The study participants will be protected against any medical complication derived from the intervention, with an insurance exclusively contracted for ADILAN (HDI Seguros, policy number 130/002/001897), registered at clinicaltrials.gov as NCT01891955.

### Design

The ADILAN study is a randomized cross-over open label dietary intervention trial in patients with T2DM who will be instructed to eat two different dietary patterns during two four-week periods separated by a six-week washout period. The procedure for screening, eligibility and recruitment is detailed in Figure 2. Schedule of enrollment, interventions and assessments can be found in Additional file 1. Detailed information about enrollment, interventions and assessments is described in Additional file 2.

**Figure 2 F2:**
[figure not shown]
Diagram flow for Alimentation and Diabetes in Lanzarote (ADILAN).

### Power calculations

The predefined primary outcomes are changes in fasting fructosamine and glucagon. In order to detect, with 80% power and at a significance level of 5%, a 26 μmol/L larger reduction in fructosamine after diet B than after diet A, 12 subjects are estimated to be required. For a 37 ng/L difference in change in fasting glucagon between the diets, 13 subjects are estimated to be required.

### Intervention

The intervention is based on two diets: a) healthy diet A (healthy diet with cereal grains and dairy products), and b) healthy diet B (healthy diet without cereal grains and dairy products). After randomization, there will be no blinding to dietary assignment for study participants, nor for those administering the interventions or assessing the outcomes. Following randomization, all subjects will receive oral and written information about their respective initial dietary intervention. Owing to the fact that all participants in both groups will start the intervention at the same time, information about the specific intervention will be provided in group sessions, one for each group before the study starts. Prior to the beginning of the second dietary period, participants will be instructed about the new dietary intervention, in group sessions. Each session will last one hour and will be performed in the meeting room at the Hospital Insular de Lanzarote after the laboratory tests. The degree of behavioral support will be the same in both interventions in order to minimize differences in motivation. Written information with dietary advice, a seven-day menu plan and food recipes are similarly formulated for both diets. The rationale behind the higher intake of whole grains, dairy and legumes in healthy diet A is based on the possible beneficial effect of those foods in the treatment of T2DM in some studies [29], and their prominent position in Spanish dietary guidelines for patients with T2DM [30]. The rationale behind the exclusion of grains, dairy and legumes in healthy diet B is based on the observed positive effects in some previous studies [21,22].

Written information consists of a detailed seven-day meal plan with five meals per day and corresponding recipes (Additional file 3). Participants will be requested to follow the menu plan as much as possible when eating away from home. They will be requested to report (in as much detail as possible, the ingredients) any meal taken which differs from what is stipulated in the menu plan. In that case, they will be encouraged to photograph the meal, and send it to one of the investigators, whenever possible.

Advice about regular physical activity will be given equally to all subjects. Specifically, they will be recommended not to change their current physical activity during the whole trial.

One of the objectives of the study is to avoid weight loss during the intervention. In order to accomplish this objective, participants will be weighed once a week in order to check for weight stability. If any participant loses ≥ 1 kg compared to baseline, a new meeting will be arranged for that person to adjust his/her meal plan. We have created different versions for both menu plans in order to provide different amounts of energy per day; specifically 1,500, 1,800, 2,000, 2,200, 2,500 and 2,800 kcal/day. All the different menu versions maintain the same macronutrient composition. Depending on body weight as measured every week, each participant will be reassigned to another (with higher or lower energy) menu plan if their body weight changes by ≥ 1 kg. The meals will be taken to the lunch room in two trolleys marked with menu A or B, respectively. Each trolley will contain the trays labeled with the participant’s name. Finally, the lunch room will be separated in two areas for menu A and B, respectively.

#### Improving patients adherence to the meal plan

Despite the notion that a healthy diet can improve glucose control, adherence to dietary advice is generally poor among patients with T2DM [31]. Moreover, the particular dietary design of this trial could increase the risk of nonadherence. In order to minimize this risk, several strategies will be adopted. To facilitate the participants eating the same approximate amount of equivalent food in every meal (expressed in grams in Additional file 3), we will supply a table of equivalence. For example, 56 grams of tinned tuna equates to a small tin of tuna and 20 grams of bread corresponds to a slice of bread. Similarly, food items such as eggs or fruits will be listed as small, medium or large. In the case of more elaborated dishes, such as stewed meat, baked tubers, soups, or creams, we will provide the participants with detailed recipe directions corresponding to four servings, so as to facilitate the task in the family context. On the first day of each intervention, the investigators will review all the assigned meals, together with the participants and their partners, to make sure that the directions are understandable and easy to follow. Previous to starting the study, subjects not included in the trial will test the meals in order to elaborate a meal plan that is understandable and easy. We will ask the participants to call one of the investigators if they have any questions regarding the meal plan. Besides this, one of the investigators will meet the participants in the lunch room at the beginning of each week to give behavioral support. Furthermore, an assistant will be present on a daily basis in the lunch room to ensure that the meals are served as planned. Also, the assistant will be asked everyday to inquire whether the participants have any difficulties following the meal plans.

#### Healthy diet A

Healthy diet A will include fruit, vegetables, fish, shellfish, lean meat, nuts, eggs, olive oil and substantial amounts of whole grains, low-fat dairy products and legumes. Macronutrient composition and fiber intake will not differ from healthy diet B. GL will also be matched to that of healthy diet B. Healthy diet A is termed ‘healthy diet with cereal grains and dairy products’. This diet is classified as ‘very healthy’ using a Spanish validated nutritional software package [32]. It is in accordance with official Spanish dietary recommendations for people with T2DM regarding macronutrient composition, dietary fiber, minerals and vitamins (Tables 1 and 2). A detailed description of each of the meals proposed during the course of one week is included in Additional file 3.

**Table 1 T1:** Dietary composition of the two healthy diets

	**Energy content, kcal (SD)**		** *P-* ****value**^ **a** ^
	**Healthy diet A**	**Healthy diet B**	
Cereals	711.4 (105.2)	0	0.001
Legumes	185.4 (185.1)	0	0.07
Vegetables	102.6 (60.2)	421.4 (130.5)	< 0.0001
Fruits	259.4 (56.1)	980.1 (183.1)	0.001
Dairy products	216.6 (53.9)	0	0.001
Meats	62.9 (62.4)	173.1 (86.6)	0.02
Fish	165.7 (90.3)	186.4 (48.5)	0.6
Eggs	49.3 (41.7)	33.2 (41.4)	0.2
Sugars and cakes	0.97 (2.6)	11.8 (28.2)	0.6
Oils and fats	245.7 (45.3)	167.1 (43.7)	0.006
Drinks	8.9 (11.5)	11.5 (6.5)	0.6
Pre-cooked food	2.2 (3.0)	3.8 (5.1)	0.6
Snacks	7.1 (18.9)	7.0 (11.5)	0.5
Sauces and dressings	12.6 (26.7)	5.6 (4.4)	0.94
Other	0.5 (1.2)	0.5 (1.2)	1.0
Total energy	2,031.3 (142.3)	2,001.7 (59.5)	0.6
Total weight	1,866.8 (300.1)	2,099.8 (184.0)	0.1

Dietary composition (kcal) of the two healthy diets, as calculated from seven-day menu plans. Total weight in grams/day.

Values are means (SD).

^a^Mann-Whitney *U*-test, except for meat, fish, oils and fats, and sauces and dressings, total energy and total weight (*t*-test).

**Table 2 T2:** Daily intake of macronutrients, micronutrients, fiber, glycemic load and index, cholesterol and water, as calculated from seven-day menu plans

	**Diet**		** *P-* ****value**^ **a** ^
	**Healthy diet A**	**Healthy diet B**	
Energy			
(kcal)	2,031 (142.3)	2,002 (59.5)	0.6
(MJ)	8.5 (0.6)	8.4 (0.2)	0.6
Protein			
g	97.2 (7.6)	93.0 (4.2)	0.2
E%	19.0 (1.8)	18.3 (1.2)	0.4
Carbohydrates			
g	245.7 (18.3)	236.7 (8.4)	0.8
E%	53.0 (3.4)	53.4 (1.5)	0.8
Fiber (g)	48.5 (10.3)	53.1 (5.7)	0.3
Glycemic load (g)	116.1 (8.0)	118.0 (11.9)	0.7
Glycemic index	47.4 (1.2)	49.8 (4.7)	0.2
Total fat (g)			
g	63.6 (12.8)	62.8 (6.9)	0.89
E%	27.6 (4.6)	27.8 (2.4)	0.95
Fatty acids			
Saturated (g)	13.3 (5.2)	10.9 (2.0)	0.3
Monounsaturated (g)	30.8 (5.7)	32.1 (4.2)	0.6
Polyunsaturated (g)	10.9 (3.0)	12.5 (2.7)	0.3
Cholesterol (mg)	257.4 (106.1)	271.4 (80.1)	0.8
Water (g)	1,395.3 (296.2)	1,708.9 (240.7)	0.05
Calcium (mg)	978.3 (123.9)	591.4 (88.6)	< 0.0001
Iron (mg)	19.9 (2.8)	18.5 (2.3)	0.3
Iodine (μg)	101.7 (27.8)	143.9 (68.1)	0.15
Magnesium (mg)	570.6 (70.7)	468.6 (49.3)	0.009
Zinc (mg)	13.6 (1.8)	9.9 (2.3)	0.006
Selenium (μg)	155.7 (23.4)	126.3 (28.8)	0.057
Sodium (mg)	1,811.9 (733.9)	1,079.3 (440.7)	0.042
Potassium (mg)	3,556.0 (305.5)	6,392.9 (575.4)	0.001
Vitamin B1 (mg)	2.2 (0.3)	1.8 (0.2)	0.004
Vitamin B2 (mg)	2.2 (0.3)	1.6 (0.2)	0.001
Vitamin B3 (mg)	45.0 (5.7)	49.0 (6.9)	0.27
Vitamin B6 (mg)	2.6 (0.6)	4.2 (0.8)	0.001
Folic acid (μg)	427.6 (133.5)	506.3 (179.3)	0.37
Vitamin B12 (μg)	6.0 (1.3)	8.6 (6.3)	0.38
Vitamin C (mg)	170.1 (46.9)	434.4 (163.5)	< 0.0001
Beta-carotene (μg)	4,233.7 (1494.5)	17,194.1 (6085.9)	< 0.0001
Vitamin A (μg)	986.3 (582.8)	3,021.1 (1027.1)	0.001
Vitamin D (μg)	5.2 (3.6)	4.8 (3.2)	0.96
Vitamin E (mg)	13.0 (5.9)	23.7 (7.4)	0.01

Values are mean (SD).

^a^*t*-test, except for carbohydrate (grams), potassium and vitamin B12 (Mann–Whitney *U*-test).

